### Work package V: quantitative data of outpatient physicians

A representative sample of outpatient physicians and medical specialists described above (WP III) will be invited to participate in a postal survey or, alternatively, an online survey. A representative sample of 6,300, approx. 50% of the physicians in NRW, will be invited to participate in the survey. The addresses will be obtained via internet searches or via the medical associations in NRW (ÄKNO und ÄKWL). We expect a response rate of approx. 15% (n = 945). The following power calculation refers to a one-way between-subjects Analysis of Variance (ANOVA) and shows that with a group size of n = 945 (with a response rate of 15%), a power of 90%, an alpha of 0.05, and a sensitivity of |d| = 0.13 (Cohen’s d = 0.13) can be achieved.

Based on the results of WP II and III, the questionnaire for the treating physicians and specialists will be developed on the basis of literature research, the results of the qualitative interviews with patients, and the results of the interviews/focus groups with physicians in these fields. The basis will be validated scales as well as the study authors’ own developments based on the qualitative work packages. In this survey, among others, specialisation, professional experience, and sociodemographic variables will be related to the self-assessment of patient conversations and (stigmatizing) behaviour (secondary hypothesis 6). The questionnaire will be subjected to a cognitive pretest before being used with caregivers in order to gain insight into the processes that occur in the respondents when answering the questions [27]. Regression analyses are planned to examine sociodemographic and other physician-related factors such as stigmatization, empathy, and working conditions with descriptive and inferential statistical methods.

With regard to the survey of physicians, difficulties may arise with regard to the willingness to participate in the survey. In order to achieve the highest possible response rate the survey will be anonymous.

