#### WP IV

WP IV was planned and has so far been carried out within the expected timeframe from the first quarter of 2022 to the end of the first quarter of 2024. Since the response rate in the first survey wave by TK-NRW was lower than expected, a second recruitment wave became necessary. 40,000 insured persons were contacted by TK-NRW and invited to participate in the online survey. 2,590 insured persons participated in the online survey.

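### Work package V: 945 physicians in total cannot give 90% power for Cohen's d = 0.13 in a one-way ANOVA; the effect-size measure and number of groups need restating

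*Protocol article*

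**What the plan says.** The section on Work package V of the protocol article plans a postal or online survey of outpatient physicians: "A representative sample of 6,300, approx. 50% of the physicians in NRW, will be invited to participate in the survey". It then says "We expect a response rate of approx. 15% (n = 945"). The power calculation "refers to a one-way between-subjects Analysis of Variance (ANOVA"), with "a power of 90%, an alpha of 0.05", and concludes that "a sensitivity of |d| = 0.13 (Cohen’s d = 0.13) can be achieved".

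The sentence calls 945 a group size, although the same paragraph derives it as the whole expected sample. It gives neither the number of ANOVA groups nor the allocation between them. The power statements for Work packages I and IV also report a |d|. The one for Work package IV is expressly for independent t-tests, and the one for Work package I compares two groups.

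**The concern.** Cohen's d compares two means. The usual effect size for a one-way ANOVA is Cohen's f, the standard deviation of the group means divided by the within-group standard deviation. For two equal groups f = d/2, so confusing the two changes the apparent sensitivity by a factor of two. A d of 0.13 also looks too small for 945 people at 90% power.

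This is the only sensitivity statement for the survey on physician characteristics. If it is wrong, a reader will credit the survey with detecting differences well below those it can reliably detect, and may give a null result more weight than it can bear.

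**Working it through.** **Inputs (Work package V).** Invited 6,300; response 15%; one-way ANOVA; power 90%; alpha 0.05; stated effect d = 0.13. Check of the sample: 6,300 × 0.15 = 945, so 945 is the total N. Number of groups k: not stated, so k = 2 to 6 with equal groups is assumed below.

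**Step 1: the stated figure, two equal groups.** The standard error of the standardised difference is √(4/945) = 0.06506. Power at d = 0.13 is Φ(0.13/0.06506 − 1.960) = Φ(0.038) = 51.5%. The exact noncentral F (f = 0.065, λ = 945 × 0.065² = 3.99) gives 51.4%. The plan states 90%.

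**Step 2: what two groups can detect.** d = (1.960 + 1.2816) × √(4/945) = 0.211. The total needed for d = 0.13 is 4 × (3.2415/0.13)² ≈ 2,490.

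**Step 3: more groups.** Read d as the distance between the largest and smallest mean. With k equal groups the largest possible f is d/2 for even k and d√(k² − 1)/(2k) for odd k, reached when the means sit at the two extremes in halves as equal as possible. Power comes from the noncentral F with λ = 945f². The last column is the detectable f divided by the largest f per unit of d (0.5 for k = 2, 4 and 6; 0.4714 for k = 3; 0.4899 for k = 5).

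| k | best-case power at d = 0.13 | f detectable at 90% | smallest d detectable at 90% |
|---|---|---|---|
| 2 | 51% | 0.106 | 0.21 |
| 3 | 37% | 0.116 | 0.25 |
| 4 | 36% | 0.123 | 0.25 |
| 5 | 31% | 0.128 | 0.26 |
| 6 | 29% | 0.132 | 0.26 |

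Other patterns of means give less power: for k = 3 to 6 the least favourable pattern gives 29%, 19%, 14% and 12%. Unequal two-group splits also lose power: 50% at 40:60, 45% at 30:70 and 36% at 20:80. Whatever the allocation, f cannot exceed d/2 = 0.065, so 51% is the ceiling.

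**Step 4: readings that might rescue the figure.**
- One-sided test, two equal groups, 945 in total: 64%. An ANOVA F test is not directional in any case.
- 945 in each of two groups: 81% two-sided (detectable d = 0.149), 88% one-sided.
- 945 in each of four groups with the most favourable pattern of means: 93%. This needs 4 × 945 = 3,780 respondents, or 60% of the 6,300 invited, against the 15% stated.
- 0.13 read as Cohen's f with 945 in total: the detectable f rounds to 0.13 only for k = 5 (0.128) and k = 6 (0.132). For k = 7 it is 0.136. Power at f = 0.13 is 91.0% for k = 5 and 88.7% for k = 6.

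**Step 5: the other power statements.** Work package I: 3.2415 × √(1/936,000 + 1/104,000) = 0.0106 (stated 0.01). Work package IV: 3.2415 × √(1/104,000 + 1/3,000) = 0.0600 (stated 0.06). In both, the d label fits the arithmetic. It fails only for the ANOVA.

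**The case against.** The best defence is that 0.13 is a correct ANOVA sensitivity with the wrong symbol, so the calculation is sound and only the label is off. That may well be so. It explains the error but leaves the printed statement wrong, and f = 0.13 corresponds to a range of means of at least d = 0.26.

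A reader might go further and take it as established that the figure is a mislabelled f. The article does not support that. It never mentions f or k, and f fits only if k is 5 or 6; with 2, 3 or 4 groups it rounds to 0.11 or 0.12. About six disciplines can be counted in the section on Work package III, but they are arranged there in two strata.

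A reader might also carry over the patient survey's response, where "2,590 insured persons participated in the online survey" out of 40,000 contacted, and conclude that the physician sample will be far smaller. That survey had a different population and a different recruiter, and it has no bearing on whether 0.13 is right for n = 945.

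The objections on weight stand. The survey addresses a secondary hypothesis, the 6,300 invitations are not derived from the 0.13, regression analyses are planned as well, and no margin or decision rule is tied to the figure. That a null result would actually be over-read is a risk, not something the article announces.

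**Conclusion.** The statement is wrong as written. With 945 as the total sample, no reading of 0.13 as a between-group d reaches 90% power. The ceiling is about 51%, and the smallest detectable d is 0.21 for two equal groups or about 0.25 to 0.26 at best for 3 to 6 groups. The stated sensitivity is therefore too favourable by a factor of about 1.6 (0.21/0.13) to 2 (0.26/0.13).

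The table assumes equal groups and, for three or more groups, the most favourable pattern of means. Relaxing either does not raise power above the two-group ceiling, so the conclusion does not depend on the unstated k. That 0.13 is Cohen's f for 5 or 6 groups is probable but unproven. Nothing here shows that the survey is too small for its purpose. The point should be corrected, but it does not touch the primary hypothesis, which rests on the claims data.

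**What to change.** Restate the sensitivity sentence with the effect-size measure and the number of groups actually used in the calculation, and describe 945 as the total expected sample.

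- If the calculation used f with 5 or 6 groups: Cohen's f = 0.13, equivalent to a range of means of at least d = 0.26.
- If a two-group contrast is meant: d = 0.21, with 472 and 473 physicians per group.
- For any other number of groups: the matching value from the table above.

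Only the authors know which k was used, so they should take it from their calculation and not choose it to fit 0.13. The cost is one sentence and a less favourable stated sensitivity. No extra recruitment or change of design is needed.

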### Participatory research

The inclusion of patients, physicians, and other scientists in the study is to be practised at several points. From the beginning of the project, an advisory board consisting of affected patients, relatives, outpatient physicians, and scientists was established. During the course of the project, the advisory board will supported the preparation of the structured guideline interviews and the questionnaires. The project results will be critically discussed with the advisory board.

### Adjustments during the project

The project started on 1 July 2020 and will have a duration of four years (ending 30 June 2024). Some modifications became necessary in the course of the project. Their implementation is described below.

#### WP I

The realization of WP I was planned from the third quarter of 2020 to the end of the first quarter of 2022. The data extraction of the TK-NRW claims data (secondary data) was complicated by TK-internal processes and this led to delays in data delivery. The secondary data will be delivered in the second quarter of 2023 and subjected to plausibility checks in the third and fourth quarter of 2023. The delay in WP I had an impact on the subsequent work packages, as it was not possible to use initial results from the routine data analyses when collecting the primary data and designing the structured guidelines and questionnaires.

#### WP II

The conduction of WP II was planned and carried out within the expected timeframe from the first quarter of 2021 to the end of the fourth quarter of 2022. The interviews were conducted via telephone (n = 29) or video conference (n = 17).

#### WP III

WP III was planned and carried out within the expected timeframe from the first quarter of 2021 to the end of the fourth quarter of 2022. Since the recruitment of GPs and their willingness to participate was very low, probably due to the COVID-19 pandemic and the resulting high workload, additional recruitment channels were used. Not only were physicians in private practice contacted by post and invited to participate in focus groups and interviews, but also the study and the importance of the focus group for the study were advertised at congresses and specialist conferences as well as via newsletters of professional associations and personal contacts. Nevertheless, it was not possible to reach the target number of 50 practising doctors in the qualitative interviews and focus groups. Recruitment was stopped when nine practising physicians had been reached. However, it is planned to offer further focus groups at in 2023.

#### WP IV

WP IV was planned and has so far been carried out within the expected timeframe from the first quarter of 2022 to the end of the first quarter of 2024. Since the response rate in the first survey wave by TK-NRW was lower than expected, a second recruitment wave became necessary. 40,000 insured persons were contacted by TK-NRW and invited to participate in the online survey. 2,590 insured persons participated in the online survey.

#### WP V

WP V was planned from the first quarter of 2022 to the end of the first quarter of 2024. Due to the persistent high workload in GP practices in the fourth quarter of 2022 in Germany, the recruitment of outpatient physicians for the quantitative survey was postponed to spring 2023. Despite the delayed recruitment of physicians in WP 5, the study team expects to complete WP 5 within the planned timeframe by the end of the first quarter of 2024 (Fig. 1).

**Fig. 1 Fig1:**
[figure not shown]
Participants and Timeline

## Discussion

Research on the somatic care situation of patients with somatic disorders and comorbid mental disorders compared to patients with somatic disorders without comorbid mental disorders is rare. On the basis of previous studies, it can be assumed that there are differences in the somatic care of patients with mental disorders and patients without mental disorders. Up to now, there are no published results of a systematic collection of primary and secondary data for Germany, especially on the utilization of healthcare services in different sectors (inpatient, outpatient) by somatically ill patients with mental comorbidity. This research gap is to be closed by the present research project. Thus, in addition to the analysis of the primary and secondary healthcare utilization data, the present research project also considers the physicians’ perspective. The strength of this project resides is its mixed methods approach, which brings together the results of qualitative and quantitative methods of primary data collection with the findings of the secondary claims data analyses.

In further studies, the recommendations for action can be implemented and evaluated. The scientific results could also be applied to other relevant care sectors (e.g. hard-to-reach persons) and other indications (e.g. multimorbidity). Another strength of the study is the recruitment of participants via a large SHI company in Germany. This makes it possible for the study team to invite a large number of insured persons and recruit them for the study.

One limitation of our approach to secondary data collection is that the project team is only working with one SHI company from NRW. Unfortunately, a cooperation with other health insurance companies was not possible during the application process, even though this was originally intended by the project team, in order to minimise selection biases considering sociodemographic differences between insure populations in different German SHIs. Due to the cooperation with the largest SHI Company in Germany and also in the federal state of NRW, however, we can minimise the selection bias as far as possible. Another limitation is that we cannot conduct primary data collection nationwide, because through cooperation with TK-NRW and the General Practitioners’ Association North Rhine, primary data can only be collected within NRW. However, it should be noted that NRW is the most populous federal state in Germany and we therefore assume that we will be able to obtain a representative sample of patients and physicians.

The transmission of secondary data was delayed several times due to internal difficulties at TK-NRW, which made adjustments necessary in the work packages, for example the linkage of quantitative data and qualitative perspectives of the mixed-methods approach and adjustments in the timeline. Thus, our strategy for data collection and analyses had to be flexible. One challenge in project implementation was the COVID-19 pandemic. No face-to-face project meetings at the beginning of the study made cooperation difficult in parts. The recruitment difficulties among providers in the qualitative work package (WP III) were severe. Alternative time-consuming recruitment methods had to be used. Nevertheless, the target of fifty participants in interviews or focus groups with healthcare providers could not be reached (WP III). Furthermore, due to the tense situation in the health system in autumn/winter 2022/2023, we will delay the recruitment in WP V of healthcare providers until spring 2023. We hope to achieve a higher response rate by delaying the recruitment of GPs and specialists in private practices until spring 2023.

The study presented here aims to derive recommendations for action based on analyses of the somatic care of patients with comorbid mental disorders, which will provide opportunities to optimize care.

## Data Availability

Not applicable.

## Abbreviations

approx.: approximately
LVR-IVF: Rhineland State Council – Institute of Health Care Research [Landschaftsverband Rheinland – Institut für Versorgungsforschung]
ÄKNO: North Rhine Medical Association [Ärztekammer Nordrhein]
ÄKWL: Westphalia-Lippe Medical Association [Ärztekammer Westfalen-Lippe]
NRW: North Rhine-Westphalia
SHI: statutory health insurance
SPSS: Statistical Package for the Social Sciences
SoKo: The Somatic care of patients with mental Comorbidity
TK: Techniker Krankenkasse, a German statutory health insurance company
TK-NRW: Techniker Krankenkasse Landesvertretung Nordrhein-Westfalen, a German statutory health insurance company in North Rhine-Westphalia
WP: Work Package
